## Abstract

**Background:**

Approximately 30% of patients with pancreas cancer have unresectable locally advanced disease, which is currently treated with systemic chemotherapy. A new treatment option of irreversible electroporation (IRE) has been investigated for these patients since 2005. Cohort studies suggest that IRE confers a survival advantage, but with associated, procedure-related complications. Selection bias may account for improved survival and there have been no prospective randomised trials evaluating the harms and benefits of therapy. The aim of this trial is to evaluate the feasibility of a randomised comparison of IRE therapy with chemotherapy versus chemotherapy alone in patients with locally advanced pancreatic cancer (LAPC).

**Methods and analysis:**

Eligible patients with LAPC who have undergone first-line 5-FluoroUracil, Leucovorin, Irinotecan and Oxaliplatin chemotherapy will be randomised to receive either a single session of IRE followed by (if indicated) further chemotherapy or to chemotherapy alone (standard of care). Fifty patients from up to seven specialist pancreas centres in the UK will be recruited over a period of 15 months. Trial follow-up will be 12 months. The primary outcome measure is ability to recruit. Secondary objectives include practicality and technical success of treatment, acceptability of treatment to patients and clinicians and safety of treatment. A qualitative study has been incorporated to evaluate the patient and clinician perspective of the locally advanced pancreatic cancer with percutaneous irreversible electroporation trial. It is likely that the data obtained will guide the structure, the primary outcome measure, the power and the duration of a subsequent multicentre randomised controlled trial aimed at establishing the clinical efficiency of pancreas IRE therapy. Indicative procedure-related costings will be collected in this feasibility trial, which will inform the cost evaluation in the subsequent study on efficiency.

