### IRE for LAPC

Irreversible electroporation (IRE) is a novel ablative method for treating solid cancers.^12^ IRE treatment destroys cancer cells using electricity. It can be delivered via an open approach involving a laparotomy and placement of probes around the cancer or via a percutaneous approach, which requires image guidance, via CT or ultrasound. Both methods require the patient to be under general anaesthesia with neuromuscular blockade. A single study using propensity score matching (PSM) reported a median OS of 21.6 months in patients with LAPC treated with induction chemotherapy followed by IRE.^13^ A systematic review on pancreas IRE therapy from 2019 reported an OS from diagnosis or treatment of up to 27 months and a morbidity rate of 30%.^14^

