## Methods and analysis

### Study design and setting

The LAP-PIE trial is a UK multicentre feasibility study that will recruit 50 patients with LAPC in whom the disease has remained localised and unresectable following FOLFIRINOX. Patients will receive 3–6 months of FOLFIRINOX prior to restaging and being assessed for study eligibility. All participants will be offered palliative chemotherapy according to standard centre protocols and half will also be offered one IRE procedure. If new agents for second-line therapy are approved by NICE prior to or during the LAP-PIE trial, these can be offered in the second-line chemotherapy arm and following IRE therapy if considered appropriate by the treating oncologist. Patients randomised to the control arm who have benefitted from initial chemotherapy with FOLFIRINOX may continue on the same regimen if this deemed appropriate by the treating oncologist. It is an open-label study. Patient enrolment is expected to last 15 months assuming a recruitment rate of 0.8 patients per site per month across seven UK centres and an opening site rate of 0.5 per month. The trial will be conducted in specialist pancreas cancer centres. IRE will be delivered across all trial centres. Interventional radiologists performing pancreas IRE in the trial will have performed a minimum of five previous pancreas or liver IRE ablations prior to administrating IRE to participants enrolled in the trial. Additional technical support will be available from manufacturers of the equipment, AngioDynamics. Figure 1 summarises the trial design and table 1 demonstrates the schedule of enrolment, interventions and assessments.

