### Outcomes

The primary objective of the LAP-PIE trial is to ascertain feasibility of such a trial concept. In particular, the ability to identify and recruit LAPC patients at the selected sites to the LAP-PIE trial will be evaluated. The primary outcome consists of recruitment rate, number of screening failures, number of patients completing study pathway as per protocol and trial withdrawal rate.

The secondary objectives of the LAP-PIE trial aim to assess the practicality and technical success rate of pancreas IRE treatment. Technical success will be determined by the interventional radiologist performing the procedure. The procedure will be deemed to be technically successful if the entire tumour has been treated based on imaging performed during the intervention. Completion and complication rates of IRE procedures will be evaluated. The proportion of patients in whom percutaneous IRE was successful, defined as no local growth on follow-up, will be determined as will the proportion of patients who became eligible for surgery following IRE and the R0/R1 resection rates in these participants. Acceptability of pancreas IRE therapy to patients and their clinicians, rate of withdrawal from the study and outcome measures including OS (measured from randomisation), PFS and QoL will be evaluated. Finally, health-related costs, including indicative costs related to health resource use in both arms, social costs of attending IRE treatment such as cost of travel to and from a tertiary centre, time off work and social support costs will be evaluated.

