### Follow-up

All patients will be clinically reviewed every 3 months during which a CT CAP will be performed. Additional imaging can be performed if clinically indicated. Other investigations will include biochemistry and haematology, CA19–9 levels, C Reactive Protein (CRP), QoL as measured by a validated questionnaire (EQ5D-5L)^28^ and a clinical review of any AEs experienced. This information will be recorded in an electronic case report form.

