### Publication and dissemination

Results from different centres will be analysed and published together following completion of the recruitment and follow-up period. This will be presented to an international conference with an interest in hepatopancreaticobiliary surgery, oncology and IR and published in a peer-reviewed journal.

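### Read naturally, the protocol ends survival follow-up 12 months after each randomisation, so the IRE arm's median OS will probably not be reached; vital status to one common cut-off would recover deaths the trial's calendar already allows

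*Protocol article*

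**What the plan says.** The abstract states: "Trial follow-up will be 12 months". The Follow-up section adds "All patients will be clinically reviewed every 3 months during which a CT CAP will be performed", and Table 1 dates its visits at 3, 6, 9 and 12 months. An undated close-out column follows, with blood tests, quality of life and complications marked. The article does not say in words whether the 12 months run per patient or from the last randomisation, nor where OS is censored.

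The Outcomes section lists OS among the secondary measures: "outcome measures including OS (measured from randomisation), PFS and QoL will be evaluated". The abstract expects the data to "guide the structure, the primary outcome measure, the power and the duration of a subsequent multicentre randomised controlled trial", and the strengths and limitations box says the later trial will be powered from this one.

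On timing, Study design and setting gives 15 months of enrolment, and Publication and dissemination says: "Results from different centres will be analysed and published together following completion of the recruitment and follow-up period".

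On expected survival, the section IRE for LAPC cites a propensity-matched study that "reported a median OS of 21.6 months in patients with LAPC treated with induction chemotherapy followed by IRE". It also cites a systematic review with OS of up to 27 months, counted from diagnosis or treatment. Both figures are for patients who received IRE. No median is given for chemotherapy alone. The trial's own OS clock starts later than diagnosis: "Patients will receive 3–6 months of FOLFIRINOX prior to restaging and being assessed for study eligibility".

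**The concern.** A 12-month window is short against the survival the protocol itself cites for IRE-treated patients. If observation of each patient stops at month 12, the Kaplan-Meier curve in the IRE arm will probably still be above 50% when it ends, and the hazard after one year will not be observed. If OS were chosen as the endpoint of the later trial, its event rate and duration would then rest on extrapolation from the first year.

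The limitation is largely avoidable. Patients randomised early will have been in the trial for up to 27 months when the results are analysed. On the natural reading, their survival status between month 12 and that date is not part of the planned data, although learning it would need no further patients or calendar time.

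**Working it through.** **Inputs from the protocol article.** 50 patients, randomised equally, so 25 per arm (Sample size calculation). Recruitment over 15 months, 0.8 patients per site per month, seven sites, opening at 0.5 per month (Study design and setting). Follow-up of 12 months (abstract, Table 1). Cited OS after IRE of 21.6 and up to 27 months (IRE for LAPC). FOLFIRINOX for 3–6 months before eligibility assessment (Study design and setting).

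**Assumptions that are not in the article.** Exponential survival; no dropout; subtraction of 3 or 6 months from 21.6 as a rough correction for the later OS clock; the range of control-arm medians.

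**Step 1: the plan's own figure.** The article gives no expected number of deaths. Its recruitment figure can be reproduced:
- Assessment of feasibility: 40 × 20% = 8 per centre per year; 8 × 5 centres × 15/12 = 50.
- Study design and setting, with sites opening at months 0, 2, …, 12: 15 + 13 + 11 + 9 + 7 + 5 + 3 = 63 site-months; 63 × 0.8 = 50.4.

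The last patient's 12-month date is therefore about month 15 + 12 = 27.

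**Step 2: is the median reached with 12 months per patient?** With true median m, S(12) = 2^(−12/m). With 25 patients and no losses, the Kaplan-Meier estimate falls to 50% or below only with at least 13 deaths, so P(reached) = P(Bin(25, 1 − S(12)) ≥ 13).

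| True median from randomisation (months) | S(12) | Expected deaths of 25 | P(median reached) |
|---|---|---|---|
| 27 | 73.5% | 6.6 | 0.6% |
| 21.6 | 68.0% | 8.0 | 3.0% |
| 18.6 (21.6 − 3) | 63.9% | 9.0 | 7.5% |
| 15.6 (21.6 − 6) | 58.7% | 10.3 | 19% |

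For the control arm, over an assumed range of medians, the same formula gives 85% at 9 months, 74% at 10, 50% at 12, 22% at 15 and 9% at 18. The dividing line is 12 months.

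**Step 3: deaths with a common cut-off at month 27.** Follow-up then runs from 12 to 27 months. With λ = ln 2 / m and uniform accrual over 15 months, expected deaths = 50 × [1 − (e^(−12λ) − e^(−27λ)) / (15λ)]. For m = 21.6, λ = 0.0321 and deaths = 50 × [1 − (0.680 − 0.420)/0.481] = 23.0. With the staggered site opening of Step 1, accrual falls later and the gain is smaller. Both are shown, taking one median for all 50 patients.

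| Median (months) | Deaths, 12 months each: 50 × (1 − 2^(−12/m)) | Deaths, common cut-off (staggered to uniform) | Increase |
|---|---|---|---|
| 15.6 | 20.7 | 26.6 to 28.6 | 29–38% |
| 21.6 | 16.0 | 21.2 to 23.0 | 33–44% |
| 27 | 13.3 | 17.9 to 19.5 | 35–47% |

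Mean planned follow-up, before allowing for deaths, is 17.4 months (staggered) or (12 + 27)/2 = 19.5 months (uniform), against 12.

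**Step 4: is the median reached with the common cut-off?** Simulation with staggered accrual (4,000 runs, 25 patients) gives about 82% at a median of 15.6 months, 67% at 18.6, 54% at 21.6 and 34% at 27.

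**The case against.** The strongest reply is that several tempting conclusions go further than the text.

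- **Both arms will miss their medians.** A reader might infer this, but the 21.6 and 27 months concern IRE-treated patients only. With a control median of 12 months or less, the median is as likely as not, or more likely, to be reached. This stands.
- **The cited figures apply directly.** They do not. The 27 is an upper value counted from diagnosis or treatment, the origin of the 21.6 is not stated, and the protocol warns that selection may explain both. Shorter true medians would make the problem smaller. This stands, and is why the range extends down to 15.6 months.
- **Later survival is discarded.** The article does not say so. It is silent on censoring and has an undated close-out column, and a fuller protocol or analysis plan may settle the matter. Month 12 per patient is the natural reading, not a stated rule.
- **The trial fails to supply what the next one needs.** The next trial's endpoint is still open, OS is secondary here, none of the four progression criteria uses it, and 12-month survival is a usable planning input. The article also gives no support for expecting an IRE effect that first appears after one year. This stands.
- **The gain is modest.** At a median of 21.6 months, the approximate standard error of the log hazard ratio, 2/√deaths, falls from 2/√16.0 = 0.50 to between 2/√23.0 = 0.42 and 2/√21.2 = 0.43. The 95% limits tighten from a factor of about 2.7 to about 2.3. Neither would size a trial alone.

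What the reply does not remove is that the extra information costs almost nothing and serves a purpose the protocol states.

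**Conclusion.** The point holds as a limitation of a secondary outcome. If follow-up is 12 months per patient, the IRE arm's median OS is unlikely to be reached: probability about 0.6–3% at the cited figures, and about 19% after subtracting 6 months of prior chemotherapy. For the control arm, the same conclusion needs a median above 12 months from randomisation, and the article gives none. The primary feasibility outcome is unaffected, and no stated figure is wrong.

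Vital status to a common cut-off would add about 29–47% more deaths over the medians examined. These sizes rest on exponential survival, no dropout, recruitment in 15 months as planned and, for the death counts, one median applied to all 50 patients. Even then, the IRE arm's median is not assured: about 54% at 21.6 months and 34% at 27.

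**What to change.** State whether the 12 months run per patient or from the last randomisation. Keep the CT and EQ-5D-5L visits to 12 months. Add that vital status will be collected for all patients to one common cut-off, 12 months after the last randomisation. Estimate OS by arm by Kaplan-Meier to that date, and report 12-month OS as well.

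Leave PFS on the scheduled-imaging window. Progression dates gathered after scheduled CT has stopped would be unevenly ascertained, possibly by arm in an open-label trial.

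The cost is one protocol sentence and one check of notes or telephone contact per surviving early recruit at close-out. There are no additional patients, scans or months of trial duration. The downside is follow-up of unequal length, which time-to-event methods handle.

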**Ethics and dissemination:**

The protocol has received approval by London-Brent Research Ethics Committee reference number 21/LO/0077.

Results will be analysed following completion of trial recruitment and follow-up. Results will be presented to international conferences with an interest in oncology, hepatopancreaticobiliary surgery and interventional radiology and be published in a peer-reviewed journal.

**Trial registration number:**

ISRCTN14986389.

Strengths and limitations of this studyThis trial is the first randomised comparison of irreversible electroporation therapy with 5-FluoroUracil, Leucovorin, Irinotecan and Oxaliplatin (FOLFIRINOX) vs FOLFIRINOX alone in patients with locally advanced pancreatic cancer (LAPC) and will aim to evaluate the feasibility of recruitment of patients with LAPC across multiple pancreas cancer specialist units in the UK.As a feasibility study, it is not powered to show effectiveness; however, it is likely that the data will help inform a larger multicentre trial.Experience in optimising recruitment, site setup and developing local radiology expertise will be crucial for the success of the subsequent trial, which will be powered from data collected during this feasibility study.A potential limitation of the study is inadequate recruitment due to competing trials recruiting patients with LAPC.

## Introduction

### Pancreas cancer and LAPC

Pancreatic cancer (PC) is one of the deadliest cancers worldwide. It has a 5-year survival rate of less than 6% and an increasing incidence.^1^ The low survival rate is mainly due to late diagnosis, as PC often remains asymptomatic until it becomes advanced. Surgery (pancreatic resection) is the only potentially curative treatment. However, only 10%–20% of patients are eligible for surgery.^2^ Approximately 30% of all patients have locally advanced pancreatic cancer (LAPC) at diagnosis and are not considered for surgical resection.^3^

### Chemotherapy for LAPC

Systemic chemotherapy is the standard treatment for unresectable PC.^4^ Despite advances in drug therapy for pancreas cancer over the last 20 years, the overall survival (OS) and progression-free survival (PFS) of these patients have not significantly improved.^5^ Furthermore, a meta-analysis reported that chemoradiation is not superior to chemotherapy alone in patients with LAPC, with comparable OS and higher rates of grade 3–4 adverse events (AEs).^6^

In the UK National Institure of Clinical Excellence (NICE) guidelines, published in 2018, recommend systemic combination chemotherapy for both locally unresectable and metastatic PC.^7^ NICE recommends first-line combination chemotherapy with 5-FluoroUracil, Leucovorin, Irinotecan and Oxaliplatin (FOLFIRINOX) in fit patients (Eastern Cooperative Oncology Group performance status of 0–1). In patients with comorbidities and restricted activities, or those unable to tolerate this regime, NICE recommends gemcitabine alone or gemcitabine-based therapy.^6^ Although FOLFIRINOX shows the best objective response in PC,^8 9^ it is associated with more frequent and severe side effects, including neutropenia, diarrhoea and peripheral neuropathy.^10^

### Repeat staging after first-line chemotherapy and possibility of resection

Staging is repeated following first-line chemotherapy for LAPC and imaging is reviewed once again regarding suitability for resection. In patients with locally advanced disease undergoing first-line treatment with FOLFIRINOX, 25.9% underwent resection, with an R0 resection rate of 78.4%; however, the long-term outcomes for these patients are not reported in the studies, and there is still a possibility of recurrence although at later date.^11^

### IRE for LAPC

Irreversible electroporation (IRE) is a novel ablative method for treating solid cancers.^12^ IRE treatment destroys cancer cells using electricity. It can be delivered via an open approach involving a laparotomy and placement of probes around the cancer or via a percutaneous approach, which requires image guidance, via CT or ultrasound. Both methods require the patient to be under general anaesthesia with neuromuscular blockade. A single study using propensity score matching (PSM) reported a median OS of 21.6 months in patients with LAPC treated with induction chemotherapy followed by IRE.^13^ A systematic review on pancreas IRE therapy from 2019 reported an OS from diagnosis or treatment of up to 27 months and a morbidity rate of 30%.^14^

### First-line, up-front chemotherapy

The timing of chemotherapy in relation to IRE therapy may influence outcome. Studies where IRE has been delivered before chemotherapy have reported only modest increases in median OS,^15 16^ whereas a systematic review evaluating the impact of IRE after induction treatment reported an OS of 27 months.^14^ This may be because chemotherapy responders who have better outcomes are being selected to undergo IRE or alternatively it may suggest that chemotherapy modifies the tumour microenvironment making it more sensitive to IRE.

### Second-line chemotherapy for LAPC

NICE recommends that patients who have previously undergone FOLFIRINOX therapy as first line should be offered Gemcitabine-based second-line chemotherapy if their cancer has progressed on FOLFIRIONOX.^17^

### Locally advanced and borderline unresectable LAPC

The definition of borderline resectable disease is controversial,^18^ whereas the definition of unresectable locally advanced disease has clear consensus, namely, the involvement of the coeliac artery or encasement of the superior mesenteric artery of more than 180° and or the involvement of the superior mesenteric vein or portal vein with no distant metastasis.^19^ Therefore, the locally advanced pancreatic cancer with percutaneous irreversible electroporation (LAP-PIE) trial will only involve patients with locally advanced disease fulfilling published criteria.

### Complications of pancreas IRE therapy

Reported complications following pancreas IRE include pancreatic fistula, venous and arterial thrombosis, arterial pseudoaneurysm and pancreatic abscess.^14^ The mean morbidity rate in the studies examined is 34% but can reach up to 62%.^20^ The average rate of severe complications (defined as greater than grade III on the Clavien-Dindo scale) following IRE is 8% but can be as high as 44%.^21^ The average procedure of related mortality rate in these studies is 3%.^12^

There are significant variations in the percentage and severity of complications reported. This difference may be due to the case selection, whether IRE is carried out during surgery (via an open or laparoscopic approach) or with image guidance in the interventional radiology (IR) suite, the treatment algorithm, the completeness of reporting from treatment centres or the experience of the radiologist and/or centre. Only two studies specifically mention the experience of clinicians delivering IRE^16 22^ and, currently, there is limited published data available exploring the number of IRE procedures performed and the relationship with outcomes.^23^

IRE is a palliative option and, therefore, its impact on patient’s quality of life (QoL) is an essential consideration. A single-centre prospective study evaluating the QoL pre and post-IRE in patients with LAPC demonstrated that IRE had no adverse effect on QoL in the short-term; however, concomitant treatment with chemotherapy after IRE as well as other inter-related factors may confound the results.^24^ We were unable to find any studies comparing QoL changes following IRE to a control group. The published data, to date, regarding the improvement in QoL in patients with LAPC undergoing IRE is weak and needs further exploration.

The current information available in the literature regarding the use of IRE in the treatment of LAPC is primarily from retrospective and prospective cohort studies. A single prospective randomised controlled trial (RCT) has recently reported on the use of IRE in LAPC with concurrent gemcitabine therapy.^25^ The authors report a survival advantage in patients treated with IRE and gemcitabine. Therefore, some evidence is available for the efficacy of IRE in LAPC; however, the LAP-PIE trial will evaluate whether this is also the case in the modern context of FOLFIRINOX chemotherapy, a regimen recommended in the UK by NICE. The LAP-PIE trial is a feasibility trial to determine whether patients would be willing to have pancreas IRE treatment, whether they would accept randomisation to IRE or standard of care chemotherapy, whether they would comply with treatment and study data collection and to collect preliminary data on efficacy end points and indicative costs related to health resources, with which to design a subsequent trial on treatment efficiency and cost-effectiveness.

